## Abstract

**Introduction:**

Urinary tract infections (UTIs) are highly prevalent and pose a significant burden among older adults. Accurate diagnosis in this population is challenging due to the high prevalence of pre-existing lower urinary tract symptoms, inability to express symptoms and asymptomatic bacteriuria. Current diagnostic tests are unreliable, often resulting in over- and underdiagnosis. A previous pilot study proposed a higher cut-off for pyuria and identified five promising biomarkers for the diagnosis of UTIs in older adults. The UTI-GOLD study aims to validate these five new biomarkers and the higher leucocyte cut-off as a diagnostic tool for UTIs in older people in a real-world setting.

**Methods and analysis:**

Between August 2024 and December 2027, an observational multicentre diagnostic accuracy study is being conducted across primary, secondary and tertiary healthcare facilities in the Netherlands and the UK. Adults ≥65 years with a suspected UTI will be considered eligible. Patients with pre-existing decision-making incapacity or an indwelling catheter will be excluded. UTI will be defined according to an international consensus-based reference standard. Biomarkers will be measured by liquid chromatography-mass spectrometry (neutrophil gelatinase-associated lipocalin, tissue inhibitor of metalloproteinase 2 and CXC motif chemokine ligand 9) and enzyme-linked immunosorbent assay (interleukin 6 and azurocidin). Pyuria will be quantified by automated microscopy and/or flow cytometry. Diagnostic accuracy measures will be calculated using the receiver operating characteristic curves, and sensitivity, specificity, likelihood ratios and predictive values will be reported for optimal cut-offs.

**Ethics and dissemination:**

The protocol was reviewed by the local Leiden University Medical Center research committee, who declared on 15 April 2024 that the medical research involving human subject act (Dutch abbreviation: WMO) does not apply to the current study (reference number nWMODIV2_2024025). The study also received approval from the NHS Research Ethics Committee in the UK (reference number 24/LO/0649).

The study findings will be published in a peer-reviewed journal, presented at academic congresses and shared with healthcare providers.

**Trial registration number:**

The study was registered at clinicaltrial.gov on the 24 September 2024 with registration number: NCT06610721.

STRENGTHS AND LIMITATIONSThe broadly defined inclusion criteria and recruitment from different healthcare settings contribute to applicability in the real world.Participation does not require any extra hospital visits, enhancing the inclusivity of frail older people.To prevent selection bias, the study also accepts urine samples that are not collected according to the preferred clean catch (mid-stream) method.A research reference standard is used to define urinary tract infections, aiming to minimise the risk of misclassification that inevitably arises due to the atypical presentation of older adults and the lack of a golden standard.The exclusion of older people with pre-existing decision-making incapacity may restrict the generalisability of the study results.

## Introduction

 Urinary tract infections (UTIs) are one of the most common bacterial infections worldwide.^1^ Especially in older adults, UTIs are a significant cause of morbidity and mortality. UTIs substantially reduce quality of life,^2 3^ and UTI-related mortality rates increased notably world-wide during 1990 and 2019 for this age group.^4^ UTIs cause a significant clinical and economical strain on healthcare facilities.^5^ Despite the high prevalence and burden, diagnosing UTIs correctly presents significant challenges, especially in older adults. Older adults with comorbidities are prone to misdiagnosis of UTIs and in turn under- or overtreatment.^6^,^8^ The diagnosis of UTIs is based on a combination of symptomatology and urinalysis results, both of which are affected by age and multimorbidity.^9^ A major diagnostic difficulty in older patients is that symptoms of UTIs can be atypical or mimicked by comorbidities. Lower urinary tract symptoms (LUTS) such as urgency, urinary incontinence and frequency are common in older adults, but are often unrelated to UTI. These symptoms are frequently caused by age-associated comorbidities such as overactive bladder, vaginal atrophy or benign prostatic hyperplasia,^10^,^12^ resulting in a low specificity of lower urinary tract symptoms with increasing age. On the other hand, the sensitivity of lower urinary tract symptoms also decreases with age. Lower urinary tract symptoms can be absent in older people with UTI, including bacteraemic UTI.^11 12^ In addition, the higher prevalence of cognitive impairment (dementia or delirium) in this population may preclude a reliable identification of symptoms.

The second diagnostic challenge is the high prevalence of asymptomatic bacteriuria (ASB) in older people. Approximately 20%–50% of older women have ASB,^13^ of which 90% have concomitant pyuria.^14 15^ This phenomenon limits the diagnostic utility of the second key component of UTI diagnosis, pyuria and bacteriuria-based urinalysis, in this patient population. Previous research in older women showed that the current pyuria cut-off level of 10 cells per µL has a specificity of only 36%.^16^ The diagnostic challenge is even greater in primary care and long-term care facilities which often have only a limited diagnostic array, such as dipsticks available. This is problematic considering that the majority of UTIs are treated in these healthcare facilities. The current inaccuracy in diagnostic UTI workup can result in both over- and underdiagnosis of UTIs. Overdiagnosis drives inappropriate antibiotic use and the development of antimicrobial resistance, while underdiagnosis can result in delayed treatment, increased morbidity and mortality, and longer hospital stays.^17^

It is therefore crucial to improve diagnostic accuracy for UTI in older adults, particularly those with comorbidities and frailty.^7 18 19^ By providing reliable diagnostic markers together with appropriate cut-off values for UTIs in this population, suboptimal or delayed treatment can be avoided, which would significantly impact disease burden and improve patient outcomes. Multiple studies have identified useful biomarkers for the diagnosis of UTI.^20 21^ A recent study conducted by our group in a well-defined cohort of older women identified five promising markers for the diagnosis of UTIs. These include neutrophil gelatinase-associated lipocalin (NGAL), interleukin 6 (IL-6), azurocidin (AZU), tissue inhibitor of metalloproteinase 2 (TIMP2) and CXC motif chemokine ligand 9 (CXCL-9).^22^ NGAL is a protein that is produced by neutrophils and epithelial cells in the urinary tract and is a marker of injury and inflammation. IL-6 is a pro-inflammatory cytokine. AZU, a heparin-binding protein, is also released by neutrophils and has been identified as a marker of sepsis. TIMP-2 is a regulator of matrix metalloproteinases. CXCL9 is a chemokine induced by interferon gamma that is involved in the recruitment and activation of T cells and natural killer cells. These biomarkers hold significant potential for a new diagnostic test. In addition to these novel biomarkers, in the same cohort, the performance of an existing diagnostic tool: the urinary leucocyte (pyuria) count was investigated. The study showed that current cut-off values for pyuria lack specificity in older patients and proposed a higher, age-specific cut-off for the diagnosis of UTI. This age-specific cut-off could improve the performance of currently available diagnostic tests by tailoring their interpretation to the specific needs of older patients.

The UTI-GOLD study aims to validate five new biomarkers and the higher cut-off value for pyuria for UTI diagnosis in older patients in different real-world healthcare settings.

## Methods

### Study design and setting

The UTI-GOLD is an investigator-initiated observational multicentre, diagnostic accuracy study. Subjects will be enrolled at hospitals (n=6, the Netherlands, UK), general practitioner offices (n=9, the Netherlands) and long-term care facilities (n=2, the Netherlands). These centres will be recruited in the Leiden/the Hague region through the Extramural Leiden Academic Network and the University Network Care sector Zuid Holland. Data will be collected between August 2024 and August 2026. The study protocol was reviewed by the local research committee at Leiden University Medical Center (LUMC), who declared that the medical research involving human subject act (Dutch abbreviation: WMO) does not apply to the current study. On the 24 September 2024, the study was registered at clinicaltrial.gov (NCT06610721).

### Patient and public involvement statement

In this study, a patient panel specifically focused on UTIs was first involved during the early stages of the study design. We invited panel members to provide feedback on the overall study and more specifically to the research question, outcome measures and feasibility of the study. They helped us identify potential barriers to participation on which the study design was adjusted. They were also involved in assessing the burden on patients and the time to participate. Regarding the dissemination of the study results, the patient panel will be involved in determining what and how information will be communicated to the public. Their involvement is essential in ensuring that the study takes the needs of patients living with UTIs into account.

### Study participants

In every participating healthcare setting, the patients will initially be approached by their attending physician and provided with the patient information sheet. The study team (research physician, research nurses) will subsequently execute the informed consent procedure and will be responsible for follow-up and data collection.

Patients aged 65 years and older, both male and female, are eligible if the treating healthcare team determines that there is a clinical indication to perform diagnostic testing for a UTI. Importantly, inclusion is aligned with the clinical decision point where a urinalysis would normally be performed to confirm or rule out an UTI.

Urinary tract abnormalities, urolithiases, autoimmune disease or any form of immune compromised status are not considered exclusion criteria. Similarly, patients who recently used antimicrobial or immunosuppressant therapy will not be excluded. These broad inclusion criteria reflect the current real-world use of urinary diagnostic testing in clinical practice. By minimising exclusions, we aim to ensure that the study population closely resembles the heterogeneous group of patients for whom these tests are routinely used. Patients with pre-existing decision-making incapacity (eg, due to advanced dementia) are excluded from participation. However, patients with temporary or reversible conditions affecting decision making (eg, delirium) are eligible if they provide informed consent during the course of the study (deferred informed consent procedure). Patients with an indwelling catheter will be excluded from the study.

### Data collection and measurements

At baseline, the patients’ demographic data, medical history, current symptoms and vital signs will be collected by a trained member of the research team. The 4 A’s test (4AT),^23^ Katz Index of independence in activities of daily living (ADL) tool^24^ and PROMIS global health scale (v1.2)^25^ will be used to measure patients’ cognitive state, independence in performing daily activities and overall health respectively.

A sterile urine container will be provided to the patient along with instructions on how to obtain a clean midstream urine sample. Subsequently, patients will be asked to provide a fresh urine sample on-site. The urine sample is processed by the laboratory as soon as possible after urine production but not later than 2 hours after urine production to ensure optimal quality for urinalysis. Follow-up via telephone and electronic patient record (EPR) will be performed at 1 and 8 weeks to collect duration of symptoms, clinical outcome, complications of the infection, hospital admission, recurrence of infection and quality of life (table 1).

**Table 1 T1:** Inclusion procedure

**Variable**	Baseline	Week 1	Week 8
Symptoms			
Medical history			
Medication use			
Vitals			
PROMIS global health scale			
4AT			
KATZ ADL scale			
Urine sample			
Complications			
Hospital admission			
Recurrence of UTI <2 months			

ADL, activities of daily living; 4AT, 4 A’s test; PROMIS, Patient-Reported Outcomes Measurment System ; UTI, urinary tract infection.

#### Sediment, culture and biomarker analyses

The collected urine will be divided into three portions after collection, one for urine sediment analysis, which includes leucocyte counts; one for urine culture; and one for biomarker analysis. For patients from participating long-term care facilities and general practitioners, all analyses will be performed in the LUMC in the Netherlands (Department of Medical Microbiology and Department of Laboratory Medicine and Clinical Chemistry). For patients presenting in participating hospitals, routine urine sediment analysis and urine culture will be performed on site, while urine for biomarker analysis will be stored locally by −70°C until biomarker analyses will be performed in batch in the LUMC.

Pyuria will be quantified by automated microscopy or flow cytometry (Sysmex UF-4000, Kobe; Japan).

For culture, 10 µL of non-centrifuged urine will be added to routine culture media and incubated overnight. A positive culture will be reported in colony forming units/mL (CFU/mL) and classified as a monoculture if ≥90% of the cultured colonies are from a single species.

For biomarker analyses, urine will be transferred into a 15 mL collection tube and centrifuged for 8 min at 3000 g at room temperature. The supernatant will be transferred into another collection tube and vortexed. The urine will be divided into six aliquots and stored at −70°C. Leftover samples will be stored frozen according to local LUMC protocol for 15 years, after which the samples will be destroyed.

Urine biomarkers will be analysed in batch using an in-house developed and validated multiplex liquid chromatography-mass spectrometry (LC-MS) and ELISA. LC-MS will be used for the biomarkers NGAL, TIMP-2 and CXCL-9, and ELISA for IL-6 and azurocidin.^22^

### Outcome measures

The primary outcomes of this study are the diagnostic accuracy of the individual urine biomarkers (NGAL, IL-6, AZU, TIMP 2, CXCL9), a combination of biomarkers and the pyuria cut-off level of 200 leukocytes/µL. This cut-off level is based on the results of the pilot study which showed that 200 leukocytes/µL resulted in specificity of 86% while maintaining a high sensitivity of 89%.^16^ For the definition of a UTI, a recently developed international reference standard will be used, whereby patients will be categorised as having a definite UTI, probable UTI, possible UTI or no UTI.^26^ This reference standard was developed in a worldwide Delphi procedure and consists of (1) local signs/symptoms including LUTS, (2) systemic signs and symptoms, (3) routine urinalysis results and (4) culture results. In this manner, a more accurate and standardised approach is used to minimise misclassification. To investigate the relationship between biomarker levels and disease severity and recurrence, the following secondary outcomes are chosen: the duration of symptoms in days, complications including bacteremia, sepsis, septic shock defined in accordance with the quick sequential organ failure assessment score, and renal or prostatic abscess confirmed by ultrasound or CT scan, lengths of hospital stay in days and the frequency of recurrence of UTI defined by international reference standard within 2 months after inclusion.

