#### Analysis of outcome measures

All statistical analyses will be performed using IBM SPSS V.29. Baseline characteristics will be summarised by standard descriptive statistics.

Areas under the receiver operating characteristics (ROC) curves for identifying UTI will be calculated to assess the diagnostic power of the individual biomarkers. For each biomarker, the optimal cut-off will be determined based on the ROC curves, and the associated sensitivity and specificity, positive and negative predictive values, and positive and negative likelihood ratios will be reported. An additional logistic regression analysis will be performed to assess the value of combination(s) of biomarkers, aiming at a minimal sensitivity and specificity of 80%. For urine leukocytes, the above-mentioned parameters will be reported for a cut-off of 200 leukocytes/µL.

Subgroup analyses will be performed to assess the performance of biomarkers in males and females, different settings (hospital, primary care setting and long-term care) and different clinical presentations (systemic symptoms vs localised symptoms). Categorical values will be compared using the Fisher exact test or Pearson χ2 test.

Additional comparative analyses will be performed to compare biomarker levels in UTI with and without systemic symptoms. To assess the correlation between biomarker levels and time to resolution of symptoms and length of hospital stay, Pearson’s correlation coefficient will be used. For the calculation of the association between biomarker levels and complications of UTI and recurrence of UTI, logistic regression will be used.

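### The 200 leucocytes/µL cut-off is judged against a reference standard that includes routine urinalysis, so index test and reference overlap; the size of the bias cannot be derived from the article

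*Protocol article*

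**What the plan says.** The Outcome measures section of the protocol article lists among the primary outcomes the accuracy of "a combination of biomarkers and the pyuria cut-off level of 200 leukocytes/µL". The same section says that the reference standard "consists of (1) local signs/symptoms including LUTS, (2) systemic signs and symptoms, (3) routine urinalysis results and (4) culture results", and that under it "patients will be categorised as having a definite UTI, probable UTI, possible UTI or no UTI".

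Three other statements bear on what routine urinalysis means here:

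- Sediment, culture and biomarker analyses divides each urine sample into three portions, "one for urine sediment analysis, which includes leucocyte counts".
- For hospital patients that section states that "routine urine sediment analysis and urine culture will be performed on site".
- The Introduction calls urinalysis "the second key component of UTI diagnosis, pyuria and bacteriuria-based urinalysis".

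Analysis of outcome measures then says: "For urine leukocytes, the above-mentioned parameters will be reported for a cut-off of 200 leukocytes/µL". It names no other reference for this analysis. The Discussion presents the consensus standard as a means of reducing misclassification and does not mention that it shares a component with one of the tests under study.

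**The concern.** An accuracy study asks how well an index test agrees with a classification made without it. Here the leucocyte count is the index test, and it also appears to feed the classification. Some of the agreement between the two could then arise because the count helped to assign the category.

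Validating the higher pyuria cut-off is one of the study's two stated aims. If the overlap matters, the study could report better accuracy at 200/µL than a pyuria-free classification would show, and a larger sample would not correct it.

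**Working it through.** **Step 1. Does the overlap follow from the text?** The article lists routine urinalysis, not the leucocyte count by name, as a component of the standard, so one inference is needed. The sediment analysis yields the leucocyte count, the hospital sediment analysis is described as routine, and the Introduction describes urinalysis in terms of pyuria and bacteriuria. Together these support the inference.

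**Step 2. Is there a figure in the plan to reproduce?** There is none for the overlap. The sample size does not depend on it:

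- Sensitivity: 1.96² × 0.76 × 0.24 / 0.10² = 70.07, and 70.07 / 0.30 = 233.6, which gives the stated 234.
- Specificity: 1.96² × 0.72 × 0.28 / 0.10² = 77.44, and 77.44 / 0.70 = 110.6, against the stated 110.

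**Step 3. Which way does the overlap push?** Take a pyuria-free classification as the comparison, with D patients with UTI and H without. Let s and c be sensitivity and specificity at 200/µL against it.

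*Rule A: pyuria is required at a level t of 200/µL or below.* A fraction f of the D patients have counts below t and drop out of the UTI group. All of them are index-negative, so they move from false negative to true negative:

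- sensitivity becomes s / (1 − f), which is at least s;
- specificity becomes (cH + fD) / (H + fD), which is at least c.

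*Rule B: pyuria upgrades patients to UTI, and those upgraded have counts of 200/µL or more.* A fraction g of the (1 − c)H false positives become true positives. With m = g(1 − c)H:

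- sensitivity becomes (sD + m) / (D + m), which is at least s;
- specificity becomes cH / (H − m), which is at least c.

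Under both rules patients move only from discordant to concordant cells, so neither measure can fall.

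**Step 4. Where does the direction stop being certain?**

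- If upgrading also applies below 200/µL, upgraded patients with counts between that lower level and 200/µL move from true negative to false negative, which works against the shift under Rule B.
- If pyuria were required above 200/µL, patients between the two levels would move from true positive to false positive.
- If a patient without pyuria is only demoted to a category that still counts as UTI, nothing moves and there is no bias.

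**Step 5. How large is it?** Under Rule A, f can lie anywhere from 0 to 1 − s, so sensitivity could lie anywhere from s to s / s = 100%. Under Rule B, g can lie anywhere from 0 to 1, so specificity could lie anywhere from c to cH / (cH) = 100%. The article gives no value for f or g, nor the level, weight or category grouping from which to estimate them.

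There is one indication that f could be small. The Introduction reports 36% specificity at 10 cells/µL in older women, so 100 − 36 = 64% of those without UTI exceed that level, and it reports concomitant pyuria in 90% of asymptomatic bacteriuria. If the standard requires pyuria only near 10/µL (an assumption), few symptomatic, culture-positive patients would fall below it.

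**The case against.** The strongest reply has four parts.

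1. **The scoring rule is not shown.** Whether pyuria is mandatory, at what level and with what weight is not in the article, nor is the split of the four categories. This stands. It limits the point to an overlap with a conditional direction.

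2. **Symptoms plus culture is not the truth.** The article reports that lower urinary tract symptoms in older people are often unrelated to UTI and that about 20%–50% of older women have asymptomatic bacteriuria. Some patients reclassified for lack of pyuria are probably correctly non-UTI. This stands too: a difference between the two classifications cannot all be called error, and the reduced version should not replace the consensus standard.

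3. **An article condenses the full protocol.** A further analysis may be specified in documents not shown. That is fair, and the point does not rest on a missing analysis. It rests on a pairing of index test and reference that the article itself fixes.

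4. **The biomarkers are not part of the standard.** This is correct. A reader might infer that NGAL and azurocidin are inflated in the same way, since the Introduction says that NGAL is produced by neutrophils and that azurocidin "is also released by neutrophils and has been identified as a marker of sepsis". A shared source suggests correlation with pyuria, which is not incorporation, and NGAL is also attributed to epithelial cells. Nor does the article plan a formal comparison of pyuria with the biomarkers, so a claim that their ranking is distorted has no planned analysis to attach to.

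**Conclusion.** The overlap is real on the article's own wording, given the one supported inference that routine urinalysis includes the leucocyte count. Relative to a pyuria-free classification, the bias can only be upward if pyuria is required at 200/µL or below, or if it upgrades patients whose counts reach 200/µL. If upgrading also acts at lower counts, the net direction is not settled. The size is unknown and may be small if pyuria is required only at a low level.

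A reader might go further and infer that the cut-off will be confirmed largely by definition, or that the pilot's accuracy at 200/µL is itself an artefact. The documents support neither. Any figure for the inflation needs an assumed share of reclassified patients, and the article does not describe the pilot's reference standard.

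**What to change.** For the pyuria outcome only:

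- Pre-specify a second classification that omits the leucocyte/urinalysis item and uses local symptoms, systemic signs and culture, scored blind to the leucocyte count.
- Report the planned accuracy measures at 200/µL against both the consensus standard and this version, using the same stated grouping of the four categories.
- Call the cut-off validated only if the two results agree reasonably, and say in advance what counts as agreement.
- State the overlap as a limitation.

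Repeating the biomarker areas under the curve against the second classification is an optional sensitivity analysis.

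The cost is one re-scoring of data already collected and one extra set of results; the target of 246 patients does not change. The drawback is that the reduced version is not the consensus standard and may admit asymptomatic bacteriuria, which is why both results are shown and neither stands alone.

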### Reflection on study design

One of the key strengths of this study is its performance across different real-life healthcare settings, characterised by broad inclusion criteria and recruitment from the three primary locations where UTIs are diagnosed: general practice, long-term care facilities and hospitals. This approach enhances validity and the applicability of the results to a wide population of older adults.

One of the largest challenges in all UTI studies, including the UTI-GOLD study, is the risk of misclassification due to the atypical presentation of older people and the lack of a gold standard for diagnosis. To minimise this risk, a recently developed consensus-based reference standard will be used to define UTIs. This standard was comprised by a national and international panel of UTI experts using a robust Delphi method, with a high degree of consensus. In the absence of a gold standard, this approach represents the most appropriate alternative to reduce classification bias and enhance homogeneity in UTI research.

The broadly defined inclusion criteria allow for the inclusion of patients with a wide variety of clinical presentations, comorbidities and frailty levels, representing a ‘real-world’ setting. Patients with an indwelling catheter were chosen to be excluded from the study since they are a separate patient population with a distinct pathophysiological mechanism and a different diagnostic approach. Similarly, patients with pre-existing decision-making incompetence will be excluded due to their inability to provide informed consent. Patients with delirium—a common symptom in older people with UTIs—will be eligible with a deferred informed consent procedure. This approach is essential, as patients with delirium represent the group in whom diagnostic uncertainty is greatest, and the use of a structured research reference standard enables their responsible inclusion in the study. It is important to acknowledge the unmet need for a reliable diagnostic tool to diagnose UTIs in patient populations that are excluded in the current study.

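### The secondary complication of sepsis and septic shock rests on qSOFA alone, which cannot identify septic shock or separate it from sepsis

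*Protocol article*

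**What the plan says.** The outcome appears in the protocol article under Outcome measures. The purpose is given as "To investigate the relationship between biomarker levels and disease severity and recurrence, the following secondary outcomes are chosen". Four secondary outcomes follow without ranking: symptom duration, complications, length of hospital stay, and recurrence within 2 months. The complications are described as "complications including bacteremia, sepsis, septic shock defined in accordance with the quick sequential organ failure assessment score", together with renal or prostatic abscess shown on imaging. No score threshold is given, and no other criterion for sepsis or for septic shock.

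Under Study participants, "patients with temporary or reversible conditions affecting decision making (eg, delirium) are eligible if they provide informed consent". The Discussion (Reflection on study design) explains that this is deliberate: "Patients with delirium—a common symptom in older people with UTIs—will be eligible with a deferred informed consent procedure", and "This approach is essential, as patients with delirium represent the group in whom diagnostic uncertainty is greatest".

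Under Data collection and measurements, at baseline "current symptoms and vital signs will be collected by a trained member of the research team", and the 4AT is named for cognitive state. After that, "Follow-up via telephone and electronic patient record (EPR) will be performed at 1 and 8 weeks", and complications are among the items collected. Under Analysis of outcome measures, complications and recurrence are each related to biomarker levels by logistic regression.

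**The concern.** An outcome definition has to be able to pick out the condition it names. qSOFA is a bedside score with three items: respiratory rate, systolic blood pressure and altered mentation. Those items are the published content of the instrument the article names; the article does not list them. None of them records vasopressor support, lactate or any other measure of perfusion. A case labelled septic shock on this score alone is therefore not shown to be septic shock.

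The population adds a second difficulty. Altered mentation is one item in three, and the study makes a point of recruiting people with delirium. A patient who is delirious at inclusion may already carry a point before anything that would be called a complication has occurred. The article does not say how this is handled.

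At stake is the analysis relating biomarkers to severity through complications. If the events in that regression are partly mislabelled, the estimated association describes something other than the named condition.

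**Working it through.** **1. The plan's own figures, to fix the scale.** Inputs from Sample size: α = 0.05, margin 0.10, specificity 72%, sensitivity 76%, prevalence 30%, dropout 5%. Formula: N = z² p(1−p) / d², divided by (1 − prevalence) for specificity or by prevalence for sensitivity, with z = 1.96.

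- Specificity: 1.96² × 0.72 × 0.28 / 0.10² = 77.4; 77.4 / 0.70 = 110.6 (stated 110).
- Sensitivity: 1.96² × 0.76 × 0.24 / 0.10² = 70.07; 70.07 / 0.30 = 233.6, so 234 (stated 234).
- Dropout: 234 × 1.05 = 245.7, so 246 (stated 246).

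The figures reproduce. None of them uses sepsis or septic shock, so the point leaves the sample size untouched. Expected UTI cases among 234 evaluable patients: 234 × 0.30 = 70.2, about 70.

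**2. The two readings of the definition.**

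| Reading | Septic shock | Sepsis |
|---|---|---|
| The phrase covers both | qSOFA, no shock element | qSOFA, with nothing stated to separate it from shock |
| The phrase covers septic shock only | qSOFA, no shock element | no definition given |

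The septic shock cell is the same in both rows. A cut-off would not repair it, because no value of a score without a vasopressor or perfusion item supplies one.

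**3. The mentation item.** Set side by side, Outcome measures names a score with a mentation item, while Study participants and the Discussion enrol delirium by design. The overlap follows from the text. Its frequency does not: the article gives no delirium rate, no rate of abnormal vital signs and no sepsis rate.

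**4. What the overlap could do, with assumed rates only.** Take 70 UTI cases. Let c be the share with true sepsis or shock, all captured, and f the share of the remaining cases labelled positive in error. True events = 70c; false events = 70(1 − c)f.

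| c (assumed) | f (assumed) | True | False | Share of labelled events that are true |
|---|---|---|---|---|
| 5% | 0% | 3.5 | 0 | 100% |
| 5% | 5% | 3.5 | 3.3 | 51% |
| 5% | 20% | 3.5 | 13.3 | 21% |
| 10% | 0% | 7.0 | 0 | 100% |
| 10% | 5% | 7.0 | 3.2 | 69% |
| 10% | 20% | 7.0 | 12.6 | 36% |

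The range runs from no effect to a large one. The table shows only that, with so few expected events, a handful of wrong labels would matter. It is not an estimate.

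**The case against.** The strongest reply is that a journal article condenses the full protocol, where thresholds and operational rules normally sit. That would answer a complaint about a missing cut-off. It does not answer this one, because the article states a definition and the instrument it names lacks the element needed.

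Several stronger readings are tempting, and the article does not support them.

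- *This is the main severity outcome.* It is one component of one of four unranked secondary outcomes. Bacteraemia and abscess in the same list do not depend on the score, and symptom duration and length of stay have their own analysis.
- *Sepsis and septic shock would be the same events.* That needs the joint reading and a single threshold. The sentence is ambiguous and no threshold is given.
- *The outcome is really the baseline vital signs.* Complications are collected at weeks 1 and 8 from the electronic patient record as well as by telephone, and a record can hold vital signs for admitted patients. The timing marks in Table 1 are not legible in the text at hand, so the schedule of vital signs cannot be inferred.
- *A large share of the events would be false.* That rests wholly on assumed rates. Patients who already lacked decision-making capacity are excluded, which removes many with chronically altered mentation. Acute delirium during infection can itself be a sign of true severity.

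One further objection stands in part: other organ-dysfunction scores, SOFA among them, also assess consciousness. Changing the score would not by itself settle how delirium at inclusion is counted, so the rule has to be written down.

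**Conclusion.** The point holds in a limited form. As written, the rule cannot identify septic shock or distinguish it from sepsis on either reading, and on the narrower reading sepsis is undefined. This rests on the quoted sentence and on the known content of the named score, and needs no assumed rate. Some score-positive cases may also reflect delirium at presentation. That follows from the enrolment policy, but its size is unknown and cannot be worked out from the article.

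The consequence is confined to the sepsis and septic shock component of the complications outcome and to the logistic regression that uses it. The primary outcomes, which begin "The primary outcomes of this study are the diagnostic accuracy of the individual urine biomarkers", do not use the score. The change is worth making before the data are analysed, because the expected events are few and the correction is cheap.

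**What to change.** In Outcome measures, replace the shared reference to qSOFA with two separate research definitions taken from the electronic patient record:

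- septic shock by recorded vasopressor need, with raised lactate where it was measured;
- sepsis by a stated acute organ-dysfunction criterion in hospital patients, with a rule for delirium already present at inclusion.

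Keep qSOFA only as a separately named severity variable at inclusion. In the analysis section, report events present at the index urine sample separately from complications arising afterwards, and use the latter in the regression on complications. These are outcome definitions for analysis and do not affect how patients are managed.

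Cost: a wording change and a few extra record fields for hospital patients, with no added visits or participants. The downside is that fewer events will count as sepsis or septic shock, so that part of the regression will be less precise.
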